## Abstract

**Background:**

Recent studies demonstrated the efficacy of S-1-based adjuvant chemotherapy administered for six months after curative surgery for stage III gastric cancer; however, it is unproven whether this type of combination chemotherapy is more effective than the standard adjuvant chemotherapy of S-1 for one year.

**Methods:**

This multicenter phase II study evaluate the efficacy and safety of adjuvant chemotherapy using S-1 plus oxaliplatin followed by S-1 for up to one year for curatively resected stage III gastric cancer in patients aged over 20 years. Treatment initially comprises oral fluoropyrimidine S-1 (80 mg/m^2^) administered twice daily for the first 2 weeks of a 3-week cycle. On day 1 of a second 3-week cycle, patients will receive 100 mg/m^2^ of intravenous oxaliplatin followed by 80 mg/m^2^ of S-1 (maximum 8 cycles). Then, the patients will receive 80 mg/m^2^ of S-1 daily for 4 weeks, followed by 2 weeks of no chemotherapy. This 6-week cycle will be repeated during the first year after surgery. The primary endpoint is relapse-free survival for 3 years and secondary endpoints are safety, including the incidence of adverse events, and grading of neuropathy with each treatment cycle. The planned sample size of 75 patients is appropriate for this trial. The data will be analyzed on an intention-to-treat basis, assuming a two-sided test with a 5% level of significance.

**Discussion:**

In contrast to previous trials, the current study involves administration of S-1 until one year after surgery in addition to prior S-1 plus oxaliplatin, and is the first study to evaluate the safety and efficacy of S-1 plus oxaliplatin followed by S-1 for up to one year in patients with curatively resected stage III gastric cancer.

**Trial registration:**

This trial is registered in the University Hospital Medical Information Network’s Clinical Trials Registry (UMIN-CTR) registration number, R000029656  (https://upload.umin.ac.jp/cgi-open-bin/ctr_e/ctr_view.cgi?recptno=R000029656). Registered January 24, 2017.

## Background

Gastric cancer is the third most commonly diagnosed cancer worldwide, and one of the leading causes of cancer-related deaths [1]. Although early gastric cancer has a good prognosis with surgical resection, advanced gastric cancer shows disease recurrence at a constant rate depending on disease stage, resulting in 5-year postoperative survival rates of 70% for stage II, 47% for stage IIIA, 29% for stage IIIB, and 15% for stage IV [2]. Therefore, adjuvant chemotherapy has been widely investigated as a potentially standard component of resectable gastric cancer therapy to improve patient outcomes [3, 4].

S-1 is an orally active combination of tegafur, a prodrug that is converted by cells to fluorouracil, gimeracil, which inhibits dihydropyrimidine dehydrogenase, and oteracil, which inhibits the phosphorylation of fluorouracil in the gastrointestinal tract, thereby reducing the toxic gastrointestinal effects of fluorouracil. Postoperative adjuvant chemotherapy using S-1 for one year has become a standard treatment in patients treated by curative gastrectomy with D2 lymph node dissection for stage II or stage III gastric cancer on the basis of results from a randomized phase III study comparing surgery plus adjuvant S-1 with surgery alone (ACTS-GC trial) [3, 5]. However, the 5-year overall survival (OS) rates in stage IIIA and stage IIIB patients receiving S-1 were 67.1 and 50.2%, respectively, which are less satisfactory compared with the rate for stage II (84.2%) [5]. Therefore, patients with stage III gastric cancer are in urgent need of more effective adjuvant chemotherapy.

Recent studies demonstrated the efficacy of S-1-based adjuvant chemotherapy administered for six months after curative surgery for stage III gastric cancer, including S-1 plus cisplatin or S-1 plus oxaliplatin [6–8]; however, it is unproven whether this type of combination chemotherapy is more effective than the standard adjuvant chemotherapy of S-1 for one year. This multicenter phase II study evaluated the safety and efficacy of S-1 plus oxaliplatin for patients with curatively resected stage III gastric cancer.

## Methods

### Study objective

The trial is conducted in accordance with the World Medical Association Declaration of Helsinki and Japanese Ethical Guidelines for Medical and Health Research Involving Human Subjects. This prospective phase II trial is planned to elucidate the efficacy and safety of adjuvant chemotherapy using S-1 plus oxaliplatin for Stage III gastric cancer. The trial protocol has been approved by the Institutional Review Board (IRB) of each participating institution and the Kochi Medical School Hospital. The protocol of this study has been registered in the University Hospital Medical Information Network’s Clinical Trials Registry (UMIN-CTR) registration number, R000029656 (https://upload.umin.ac.jp/cgi-open-bin/ctr_e/ctr_view.cgi?recptno=R000029656).

### Study endpoints

The primary endpoint is relapse-free survival (RFS), and the secondary endpoints are overall survival (OS) and safety (the incidence of adverse events and grading of neuropathy in each treatment cycle).

### Eligibility criteria

Patients with resectable gastric cancer diagnosed as pathological stage III according to the Japanese Classification of Gastric Carcinoma [9] who satisfy the inclusion criteria and do not meet the exclusion criteria as described below will be recruited as subjects.

### Inclusion criteria

Histologically proven, Stage III resectable gastric adenocarcinoma according to the Japanese Classification of Gastric Carcinoma.D2 or more extensive lymph-node dissection with R0 surgery (with the result of no residual tumor)No hepatic, peritoneal, or distant metastasis; no tumor cells in peritoneal fluid on cytological analysis.Age of 20 years and over.Performance status of 0–1 according to the Eastern Cooperative Oncology Group (ECOG) scale.Patients who received surgery during the previous 6 weeks, being possible per-oral administration.No previous treatment for cancer except for the initial gastric resection to remove the primary lesion.Adequate organ function during the previous 14 days.All patients agree to participate in the clinical study through informed consent.

### Exclusion criteria

Synchronous or metachronous malignant disease, or multicentric cancer.Serious postoperative morbidity such as serious infection, anastomotic leakage, or gastrointestinal bleeding.Serious concurrent disease such as intestinal palsy, small bowel obstruction, interstitial pneumonia, pulmonary fibrosis, uncontrollable diabetes mellitus, heart failure, renal failure, liver cirrhosis, or hepatic failure.Obvious active infectious disease.Positive for hepatitis B surface antigen or hepatitis C virus antibody.Continuous treatment with steroids.Serious diarrhea.A medical history of serious allergy to any drug.Ascites beyond the pelvic cavity or pleural effusion.Clinical suspicion or previous history of metastasis to brain or meninges.Taking flucytosine or phenytoin.Clinical indication for warfarin potassium.Sensory neuropathy caused by any drug.A history of blood transfusion or administration of granulocyte colony-stimulating factor within 3 weeks before enrollment.Women who are pregnant or hope to become pregnant during the study period.Patients judged inappropriate for the study by their physicians.

### Treatment methods

S-1 will be given orally twice daily for the first 2 weeks of a 3-week cycle, at a dosage of 80 mg/day for a body surface area (BSA) less than 1.25 m^2^, 100 mg/day for BSA ranging from 1.25 m^2^ to less than 1.5 m^2^, and 120 mg/day for BSA of 1.5 m^2^ or greater. On day 1 of the second 3-week cycle, patients will receive 100 mg/m^2^ of intravenous oxaliplatin followed by 80 mg/m^2^ of S-1 (for a maximum of 8 cycles). Then, the patients will receive 80 mg/m^2^ of S-1 daily for 4 weeks, followed by 2 weeks of no chemotherapy. This 6-week cycle will be repeated during the first year after surgery.

### Registration

Eligible patients will be centrally registered within 42 days of surgery. Physicians or coordinators will send a Case Registration Form to the registration center, located at the Cancer Treatment Center, Kochi Medical School Hospital, with all the required items filled out. Accrual of patients began in March 2017.

### Statistical analysis

The primary endpoint of RFS is defined as the length of time from the surgery to the date that the patient survives without any signs or symptoms of that recurrence, whichever is sooner. The primary objective of this trial is to evaluate the RFS of using S-1 plus oxaliplatin as the adjuvant chemotherapy for resected stage III gastric cancer. The three years RFS will be calculated point estimates and 2-sided 90% confidence intervals. Cumulative RFS curves will be constructed as time-to event plots by the Kaplan-Meier method. With regard to secondary endpoints, OS, which is defined as the time from the date of surgery to date of death from any cause, will be evaluated according to the method of analysis of the primary endpoint. For the analysis of safety, Fisher’s exact test will be used if necessary, and the exact 95% confidence intervals for the binomial distribution will be estimated.

### Sample-size calculation

According to the ACTS-GC trial, 3-year RFS in patients with stage III gastric cancer who underwent adjuvant chemotherapy using S-1 was 62.3% (68.0% in stage IIIA and 49.8% in stage IIIB) [3]. Survival analysis of adjuvant chemotherapy with S-1 plus cisplatin for stage III gastric cancer demonstrated 74.1% RFS [8]. Under the hypothesis of a threshold 3-year RFS of 62% and an expected 3-year RFS of 75%, at 3 years follow-up after registration, 62 patients in total are needed to ensure an 1-sided alpha value of 0.05, and statistical power of 80% [10]. Considering the likelihood of some ineligible cases in the whole setting outlined above, the total sample size is set to 75.

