### Follow-up

During treatment under this protocol, patients will undergo a physical check-up and a blood examination before every drug administration. During and after finishing the protocol treatment, patients are physically examined for recurrence, and tumor markers (CEA, CA19–9, CA125, and CA72–4) are measured every 3 months for 3 years. Abdominal computed tomography scans and chest radiographs are obtained every 3 months for 3 years. Adverse events will be graded according to the National Cancer Institute’s Common Terminology Criteria for Adverse Events (version 4.0). Adverse events will be documented during chemotherapy and for 28 days after the last dose of study medication. Registered patients will be followed up to confirm the presence or absence of recurrence and survival status for 5 years after accrual of the last patient.

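### The 80% power claimed for 62 patients does not belong to the stated primary analysis (3-year RFS with a 90% CI), whose power at 62 is about 70%

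*Protocol article*

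**What the plan says.** The Sample-size calculation section sets a "threshold 3-year RFS of 62% and an expected 3-year RFS of 75" per cent, judged "at 3 years follow-up after registration", and concludes that "62 patients in total are needed to ensure an 1-sided alpha value of 0.05, and statistical power of 80% [10"]. It names no test beyond the cited reference. It then raises the number: "Considering the likelihood of some ineligible cases in the whole setting outlined above, the total sample size is set to 75".

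The Statistical analysis section describes the primary analysis: "The three years RFS will be calculated point estimates and 2-sided 90% confidence intervals". It adds that "Cumulative RFS curves will be constructed as time-to event plots by the Kaplan-Meier method". It mentions no one-sample log-rank test and no exponential model.

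On timing, the Registration section gives only the start ("Accrual of patients began in March 2017"), not the length of accrual. The Follow-up section has patients followed "for 5 years after accrual of the last patient".

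**The concern.** The lower limit of a two-sided 90% interval, compared with 62%, is a one-sided 5% test. The planned interval and the stated alpha therefore agree, and the power of that test can be calculated from the article's own figures. If every patient is followed to 3 years, the Kaplan-Meier estimate at 3 years is the simple proportion event-free, and events after year 3 add nothing to it. A one-sample comparison of 62% with 75% at one-sided 5% and 80% power ordinarily needs about 80 patients, not 62.

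This is the primary endpoint of a single-arm trial. If power is lower than stated, a regimen that truly reaches 75% fails to clear the threshold more often than the 1 in 5 that readers are told, and such a miss could be taken as evidence against the regimen.

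**Working it through.** **Inputs.** p0 = 0.62, p1 = 0.75, one-sided alpha 0.05 (z = 1.645), power 0.80 (z = 0.842), n = 62 and enrolment 75 (Sample-size calculation); two-sided 90% interval at 3 years (Statistical analysis). Assumption: 3-year status is known for everyone analysed.

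**Step 1. Trying to reproduce 62 at a fixed 3-year time point.**
- Null and alternative variance: n = [(1.645·√(0.62·0.38) + 0.842·√(0.75·0.25)) / 0.13]² = 80.0.
- Arcsine: 78.2, so 79.
- Wald (variance at 75% only): (1.645 + 0.842)²·0.1875 / 0.13² = 68.6, so 69.
- Exact binomial with alpha at most 5%: 80% power is first reached at n = 84 (cut-off 60/84, alpha 4.6%, power 81.2%); n = 81 just misses, at 79.97%.

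None gives 62.

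**Step 2. Power at n = 62.**
- Null and alternative variance: Φ[(0.13·√62 − 1.645·√0.2356) / √0.1875] = 69.9%.
- Wald: Φ[0.13·√(62/0.1875) − 1.645] = 76.4%.
- Exact, by the cut-off that each type of 90% interval implies:

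| Interval | Success at | Exact one-sided alpha | Power at 75% |
|---|---|---|---|
| log-log, Clopper-Pearson | 46/62 | 3.0% | 62.4% |
| plain, logit, arcsine, Wilson | 45/62 | 5.4% | 72.6% |
| log | 44/62 | 9.1% | 81.2% |

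Only the log-transformed interval reaches 80%, and its true one-sided error is nearly twice the stated 5%.

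**Step 3. Power at n = 75, all analysed.**
- Normal approximation: 77.5%. Wald: 83.0%.
- Exact, 54/75 (72.0%): alpha 4.6%, power 77.1%. This is the cut-off for the log-log, logit, arcsine, Wilson and Clopper-Pearson intervals.
- Exact, 53/75: alpha 7.5%, power 84.2%. This is the cut-off for the plain and log intervals.

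**Step 4. Where 62 could come from.** Take exponential RFS, with hazard ratio ln 0.75 / ln 0.62 = 0.602. For the one-sample log-rank test, let v1 be the probability of an event under the alternative over the whole follow-up, and v0 = v1/0.602 the expected events per patient at the null hazard. Then n = (1.645·√v0 + 0.842·√v1)² / (v0 − v1)².
- Exactly 3 years of follow-up each: v1 = 0.250, v0 = 0.415, n = 80.2.
- Assumed uniform accrual plus 3 years of follow-up: 70.3 with 1 year of accrual, 63.1 with 2 years, 61.6 with 2.25 years, 57.5 with 3 years.
- An exponential test on the cube-root hazard with 2 years of accrual plus 3 years of follow-up: 61.5, so 62.
- Power of the one-sample log-rank test with 2 years of accrual: 79% at 62 patients and 87% at 75.

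So a number near 62 is what a whole-curve test would give, provided that events after year 3 in early-enrolled patients count and that accrual lasts about 2 years.

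**The case against.** The strongest reply is that 62 is a normal result of a standard survival design. The sizing rests on a cited reference that is not at hand, and 3 years after registration can be read as the minimum follow-up once accrual closes. On that reading Step 4 lands on 61.5 to 63.1, and the full protocol may well state the test and the accrual period. This stands as far as it goes. A reader might infer from Step 1 that the sample size was miscalculated; the article does not support that. What the reply does not rescue is the pairing: the analysis the article describes is the 3-year estimate with its interval, which makes no use of later events, and the 80% is presented as the power of the trial so analysed.

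A reader might also infer that a truly effective regimen would miss the threshold in about 3 of 8 trials (1 − 0.624). That is the worst case. It belongs to the 46/62 cut-off, whose alpha is 3.0%, and is partly an effect of discreteness: one more patient (46/63, alpha 4.5%) brings power to 70.1%. The article does not name the RFS interval and mentions exact intervals only for safety, so about 70% is the fairer summary.

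Finally, 75 patients are to be enrolled and the Abstract specifies an intention-to-treat analysis. If all 75 are analysed, the shortfall is about 3 points at a rule holding 5%, and none by the Wald formula. That limits the practical damage. But the article introduces the extra 13 patients as cover for ineligible cases, and the 80% is claimed at 62.

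**Conclusion.** The point holds as a mismatch between the sizing and the stated primary analysis. The planned 3-year RFS estimate with a 90% interval has about 70% power at 62 analysed patients (range 62% to 76% by method, leaving aside the log interval, which does not hold 5%). It needs about 80 patients for 80% power (69 by Wald, 84 exact). With all 75 analysed, power is about 77% at one-sided alpha 4.6%.

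These figures assume complete 3-year follow-up and the one-sided 5% level of the Sample-size calculation section, which the 90% interval matches. The whole-curve figures also assume exponential RFS and an accrual length that the article does not give. The evidence does not show that 62 is an arithmetic slip, nor that more patients must be enrolled. Severity is moderate: a stated property of the primary analysis is wrong as written, but the planned enrolment covers most of the gap.

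**What to change.** Keep enrolment at 75 and align the two sections in one of two ways.

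(a) Keep the planned analysis and restate its power. Say that the 3-year RFS with a two-sided 90% interval has about 70% power if only 62 patients are analysable and about 77% if all 75 are analysed (success at 54 or more of 75 event-free, one-sided alpha 4.6%). Say too that the second figure uses the whole 13-patient margin reserved for ineligible cases. Name the interval type, since it sets the cut-off (54/75 does not apply to the plain or log interval).

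(b) Name the one-sample log-rank test against an exponential null with 62% RFS at 3 years as the primary test. State the accrual period it assumes and give its power: about 79% at 62 with an assumed 2-year accrual. Report the 3-year RFS and its 90% interval as the estimate.

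Under (a) the stated power becomes less favourable; under (b) the primary test changes, so it should be settled before outcome data are examined. Neither needs more patients.

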### Follow-up

During treatment under this protocol, patients will undergo a physical check-up and a blood examination before every drug administration. During and after finishing the protocol treatment, patients are physically examined for recurrence, and tumor markers (CEA, CA19–9, CA125, and CA72–4) are measured every 3 months for 3 years. Abdominal computed tomography scans and chest radiographs are obtained every 3 months for 3 years. Adverse events will be graded according to the National Cancer Institute’s Common Terminology Criteria for Adverse Events (version 4.0). Adverse events will be documented during chemotherapy and for 28 days after the last dose of study medication. Registered patients will be followed up to confirm the presence or absence of recurrence and survival status for 5 years after accrual of the last patient.

## Discussion

Chemotherapy using S-1 plus oxaliplatin has showed promising efficacy against advanced gastric cancer in several large trials [11–13]. This trial is a multicenter prospective phase II study to evaluate the efficacy and safety of adjuvant chemotherapy using S-1 plus oxaliplatin followed by S-1 monotherapy for up to one year for curatively resected stage III gastric cancer. A recent study suggested that an 8-week cycle of adjuvant chemotherapy using S-1 and oxaliplatin was manageable and safe with optimal dose reduction and delay in 62 patients with stage III gastric cancer [6]. In contrast to this previous trial, the current study involves administration of S-1 until one year after surgery in addition to prior S-1 plus oxaliplatin, and is the first study to evaluate the safety and efficacy of S-1 plus oxaliplatin followed by S-1 for up to one year in patients with curatively resected stage III gastric cancer.

The ACTS-GC trial demonstrated that the addition of S-1 improved the OS rate, with a low incidence of adverse events and good compliance [3], while the CLASSIC trial indicated that adjuvant capecitabine and oxaliplatin improved 3-year disease-free survival compared with surgery alone in gastric cancer patients [4]. Studies in Japan also showed the feasibility of adjuvant chemotherapy using capecitabine and oxaliplatin in patients with stage II or III gastric cancer who underwent curative gastrectomy [14]. Although adjuvant therapy with S-1 plus cisplatin is also feasible [8], S-1 plus oxaliplatin therapy has several benefits including unnecessary hydration due to low renal toxicity. However, the evidence on which postoperative adjuvant chemotherapy has been established as standard therapy for the treatment of locally advanced gastric cancer remains under debate. The results of this study will therefore play an important role in identifying more effective adjuvant chemotherapy for patients with stage III gastric cancer in the near future.

One limitation of this trial is the non-randomized study design, which has known inferential deficiencies. However, the study design is appropriate for assessing the primary endpoint of RFS rate at three years in a limited number of patients to explore putative evidence of the adjuvant chemotherapy in the postoperative patients after gastrectomy for gastric cancer.

## Abbreviations

BSA: Body surface area
ECOG: Eastern Cooperative Oncology Group
IRB: Institutional Review Board
OS: Overall survival
RFS: Relapse-free survival
UMIN-CTR: University Hospital Medical Information Network’s Clinical Trials Registry
